### Efficacy

**Blood loss at 2 hours**: Descriptive statistics for maternal blood loss at 2 hours post-partum and total blood loss will be presented in tabular form with mean, median, standard deviation and range (minimum and maximum) as appropriate. Comparisons across groups will be done using the analysis of variance.

**Clinical diagnosis of PPH**: Number (%) of women in each randomised group will be presented.

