^. PK modelling of the oral administration of 4 g of TXA resulted in a plasma concentration of 10 mg/L within 15 min (data on file). If absorption was similarly rapid in pregnant women, this would strongly suggest the IM and oral routes as potential alternatives to IV use.

Recently, the Trauma-INTACT trial (ClinicalTrials.gov:
NCT03875937) assessed the PK of TXA administered intramuscularly in bleeding trauma patients
^
14
^. The study found that the time to reach therapeutic concentrations of 10 mg/L after intramuscular injection of 1 g TXA was within 15 min. Additionally, it was well tolerated with only mild injection site reactions and no serious adverse events reported. The PharmacoTXA trial (ClinicalTrials.gov:
NCT03777488) has assessed the PK of TXA administered intramuscularly or orally in healthy volunteers. An ongoing RCT called TRACES (TRAnexamic Acid to Reduce Blood Loss in Hemorrhagic CESarean Delivery) aims to assess the PK and pharmacodynamics (PD) effects of two doses of TXA (0.5 and 1 g) injected intravenously in women with an ongoing PPH after delivery
^
15
^.

Physiologic changes induced by pregnancy and childbirth
^
16
^ may alter the PK and PD properties of medicines, in particular due to the increase in renal elimination clearance and volume of distribution.

PPH can occur without warning in most women. However, some risk factors such as multiple pregnancy, macrosomia or previous PPH, are known to be associated with an increased risk of PPH
^
17,
18
^.

In this study we will assess the PK, PD, safety and efficacy of TXA administered by IV, IM or oral routes in women giving birth by caesarean section (CS) with at least one risk factor for PPH. Blood samples will be taken from the women immediately before the administration of TXA (1 hour before CS) and at different time points during 24 hours after receipt of intervention. Blood samples from the umbilical cord after clamping and from newborns (obtained from the sample taken for routine heel prick test) will be taken to measure the amount of TXA transferred from the mother to the neonate via the placenta. The efficacy of the different routes of TXA administration in preventing blood loss, reducing fibrinolytic activity, and the safety of the interventions will be evaluated.

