### Description of investigational product and justification of the dosage, route of administration, administration schedule and treatment duration

In this study, women will be randomised to four groups:

1.
**IV TXA GROUP:** 30 women will receive 1 g of TXA by IV route. IV TXA treatment rapidly achieves the plasma levels of TXA needed to inhibit fibrinolysis and prevent excessive bleeding. Pharmacological research has shown that an IV dose of 1 g TXA maintains therapeutic plasma levels for around 3 hours, the period when the risk of bleeding is greatest
^
12,
19
^. However, the TXA PK and PD in pregnant women has not been described so far.2.
**IM TXA GROUP:** 30 women will receive 1 g of TXA by IM route. Studies of IM TXA in healthy volunteers report good absorption and no adverse effects
^
11,
12
^. The dose will be given as two 5 mL (0.5 g each) injections into the thigh (rectus femoris or vastus lateralis) or buttocks (gluteal muscles) muscles, depending on a clinical assessment of muscle mass
^
12
^. The 1 g dose (10 mL) is divided to reduce the volume injected (5 mL is considered the upper limit)
^
20
^. The injections will be given using the most appropriate needle size for IM administration from the sites stock (1" between 19 - 25 gauge and from 1 ½ inches up to 3" for large adults) using the Z-track method to seal the medication in the muscle
^
20
^.3.
**TXA SOLUTION ORALLY:** 30 women will receive 4 g of TXA oral solution. The dose was selected because of the 50% oral bioavailability and because previous and preliminary PK data show that the absorption through the oral route is much slower than through the IV or IM routes, with much lower maximal concentration (Cmax)
^
12,
13,
19,
21
^. Therefore, higher doses are needed to reach therapeutic levels, according to simulations. The oral route (tablets or solutions) is well characterised
^
22–
24
^, but oral TXA PK and PD in pregnant women have not been described so far.4.
**NO TXA CONTROL:** 30 women will receive no TXA and will be the control group for PD, blood loss and safety data.

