### Secondary objectives

•To assess the effect of the three routes of TXA administration on D-dimer concentration in blood samples.•To assess the concentration of TXA that crosses the placenta into the neonate via the three routes of administration.•To assess clearance of any TXA in neonate.•To assess the safety of the three routes of TXA administration.•To assess the effect of the three routes of TXA administration on postpartum bleeding.

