### Primary endpoint

Blood TXA concentrations over time in pregnant women.

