### Secondary endpoints

•Blood concentrations of D-dimer over time•TXA concentration in umbilical cord and neonate after birth•Local reactions at IM injection sites•Adverse events (maternal and neonate)•Neonate status Apgar score•Measured blood loss from start of CS to 2 hours after•Clinical diagnosis of PPH

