### Randomisation

After collecting baseline data, enrolled participants will be randomised into one of the four groups described in “Description of investigational product and justification of the dosage, route of administration, administration schedule and treatment duration”. The sequence for each dosing cohort will be created using computer-generated random numbers, using blocking to ensure the required balance in the allocation of participants to treatment arms. The allocation ratio will be 1:1:1:1. 

An IT coding expert supported by a statistician who are not involved in the conduct of the trial will prepare the randomisation codes. Eligibility will be confirmed and randomisation done via an online database. Once the code is generated, the trial intervention will be prepared and administered by a trained trial team member. Participants and all trial staff will be blind to treatment allocation until randomisation is completed.

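### The only inferential analysis of blood loss is a four-group analysis of variance, which estimates no route's effect against the no-TXA control that the bleeding objective calls for

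*Protocol article*

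**What the plan says.** Secondary objectives sets the question: "To assess the effect of the three routes of TXA administration on postpartum bleeding". Background says much the same: "The efficacy of the different routes of TXA administration in preventing blood loss, reducing fibrinolytic activity, and the safety of the interventions will be evaluated". The description of the treatment groups fixes the reference arm: "30 women will receive no TXA and will be the control group for PD, blood loss and safety data". Secondary endpoints lists one measured blood-loss endpoint: "Measured blood loss from start of CS to 2 hours after".

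In the Efficacy section, a paragraph labelled as concerning loss at 2 hours begins: "Descriptive statistics for maternal blood loss at 2 hours post-partum and total blood loss will be presented in tabular form". Its only inferential sentence is: "Comparisons across groups will be done using the analysis of variance". Clinical diagnosis of PPH is tabulated by group without a test.

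Blood loss is not what the trial is built on. The primary endpoint is "Blood TXA concentrations over time in pregnant women", and the sample size calculation rests on the precision of pharmacokinetic parameters. Randomisation states: "The allocation ratio will be 1:1:1:1".

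**The concern.** The objective needs three quantities: the blood-loss difference from no TXA for IV, for IM and for oral. The stated method gives one p-value for the hypothesis that all four group means are equal. It treats no group as the reference, so the arm recruited as the blood-loss control has no special role in the analysis. A significant result could come from a gap between two TXA routes with neither distinguishable from no TXA. A non-significant result would not show how large a benefit or harm of any route remains compatible with the data.

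The Efficacy section also describes total blood loss beside the 2-hour quantity. It is not a listed endpoint, the section gives it no window, and nothing says how it ranks against the listed one.

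A results paper that followed the section literally would have group summaries and an omnibus p-value under an efficacy heading, with no estimate of any route's effect. Readers interested in IM or oral TXA would have to build that comparison themselves.

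**Working it through.** **Inputs from the protocol article.** Four groups, equal allocation, 30 women per group (4 × 30 = 120); no TXA as control for blood loss; analysis of variance across groups. There is no stated significance level, power or error rate for blood loss, so there is no figure of the plan's own to reproduce here.

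**Assumptions.** Normal errors with a common SD, 5% two-sided level, 120 − 4 = 116 error degrees of freedom. Effects are in SD units because the protocol gives no SD for blood loss.

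**1. What the F test responds to.** Its power depends on the means only through λ = n × Σ(mean of group − grand mean)², with n = 30.

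| Route means minus no TXA (SD) | λ | F test significant | At least one route differs from control (Dunnett) |
|---|---|---|---|
| All three −0.5 | 30 × (3 × 0.125² + 0.375²) = 5.625 | 47% | 57% |
| One −0.5, two 0 | 30 × (0.375² + 3 × 0.125²) = 5.625 | 48% | 35% |
| Two −0.5, one 0 | 30 × (4 × 0.25²) = 7.5 | 61% | 49% |
| −0.35, +0.35, 0 | 30 × (2 × 0.35²) = 7.35 | about 60% | – |

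The percentages are simulated, so 47% and 48% differ only by simulation error. The first two rows have the same λ: the F test cannot tell a benefit of all three routes from a benefit of one. In the last row, about 49% of the significant F tests come with no route differing from control by Dunnett's test. In the one-route row the share is about a third.

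**2. What the route-minus-control intervals would look like.** From the same model, half-width = critical value × SD × √(2/30), and √(2/30) = 0.258.

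- Unadjusted: 1.98 × 0.258 = 0.51 SD.
- Dunnett, three comparisons with control: 2.38 × 0.258 = 0.61 SD.

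**3. Precision at this size.** The difference detectable with 80% power is (z for the level + 0.84) × 0.258. This is (1.96 + 0.84) × 0.258 = 0.72 SD unadjusted, and (2.39 + 0.84) × 0.258, about 0.84 SD, with Bonferroni at 5%/3 = 1.67% each. Intervals would make this imprecision visible; an F-test p-value does not.

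**4. Error rate of the tests as stated.** If the analysis of variance covers only 2-hour loss, there is one test at 5%. If it covers both quantities and they were independent, the rate is 1 − 0.95² = 9.75%. Simulation with correlation gives 9.1% at 0.5, 8.2% at 0.8, 7.1% at 0.9 and 6.5% at 0.95. If total loss contains the 2-hour loss, a high correlation is likely, so about 6.5–8%.

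**The case against.** The strongest reply is that this is a pharmacokinetic trial. Blood loss is secondary, the sample was not sized for it, PPH is only tabulated, and the Discussion does not claim that any route reduces bleeding. Contrasts and multiplicity rules for such an outcome are commonly left to the analysis plan, which is not shown. The group tables will contain sample sizes, means and SDs, so anyone can work out each route's difference from control.

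Much of this stands, and it limits the weight of the point. It does not remove it: the protocol did choose a method, and that method does not answer its own objective. Leaving readers to derive the differences is not the same as planning to report them.

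A reader might infer that no outcome or comparator is fixed. The article does not support that. One measured blood-loss endpoint is listed, the Efficacy paragraph is labelled for 2-hour loss, and the no-TXA arm is named as control. Only the contrast linking them is absent.

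A reader might also infer that the planned tests run well above 5%. That does not follow either. The stated tests give 5% or about 6.5–10%, depending on the reading. Rates of 12% (three unadjusted route-versus-control tests on one quantity) up to 36% (all 12 pairwise tests on both) belong to contrasts that the article does not plan. Route-versus-control contrasts made only after a significant F test give about 4% for one quantity and 5.3–7.8% for both.

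Finally, Dunnett's test is not uniformly better: it rejects less often than the F test when only one or two routes work. The case with routes 0.35 SD either side of control is constructed to show the mechanism; the protocol does not predict it.

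**Conclusion.** The point holds as a mismatch between objective and analysis. The only stated inference on blood loss is an omnibus comparison that estimates no route's effect against the named control and can be significant through differences between TXA routes. The addition of total blood loss, unlisted and without a window in that section, is a smaller defect of the same paragraph.

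The practical size is modest. No primary conclusion depends on it, and at 30 per arm each route-versus-control difference carries an interval of roughly ±0.5 to ±0.6 SD. The figures rest on normal errors, equal SDs, full groups of 30 and a 5% level that the article does not state. That the F test gives no route-versus-control estimate depends on none of these. The change is worth making because it is nearly free, but it concerns estimation and reporting, and there is no demonstrated loss of error control.

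**What to change.** In the Efficacy section, or in the analysis plan with a reference from it:

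- Name the listed endpoint, loss from the start of CS to 2 hours after, as the blood-loss outcome for this objective.
- Report three mean differences from the same linear model, IV, IM and oral each minus no TXA, with 95% confidence intervals, preferably simultaneous by Dunnett's method.
- Keep the F test as a supporting result.
- Define total blood loss, and label it and the route-versus-route differences as exploratory.

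This takes a few sentences, with the same data and model and no extra participants. The simultaneous intervals are about 20% wider than unadjusted ones (0.61/0.51 = 1.20). If Dunnett's test were read as the test of any effect, it would have less power than the F test when one route works (35% against 48%) or two work (49% against 61%), and more when all three do (57% against 47%), at 0.5 SD. Keeping the F test beside the estimates limits that loss.

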### Interim analysis

There are no planned interim analyses.

### Procedure(s) to account for missing data

If one or more blood samples are not collected, the reason for this will be recorded in the CRF.

Individual missing covariate data will be ignored in the PK model.

## Data management

### Data collection

Information required in the research protocol will be collected first onto a paper CRF and transferred to an electronic case report form (eCRF). The CRF can be viewed at
https://ctu.lshtm.ac.uk/woman-ptxa/. Anonymization of the participants will be ensured by using the trial participant’s screening number as their unique ID. This will be recorded on each document needed for the research.

### Data confidentiality

The persons responsible for the quality control of the study will take all necessary precautions to ensure the confidentiality of information relating to the IMP, the study, the study participants and in particular the identity of the participants and the results obtained.

These persons, as well as the site investigators themselves, are bound by professional secrecy.

During and after the clinical study, all data collected about the study participants and sent to LSHTM CTU by the investigators (or sent to other collaborators) will be anonymised.

Under no circumstances will the names and addresses of participants be shown.

The trial will comply with relevant Data Protection regulations including the European Union General Data Protection Regulation.

The Sponsor will ensure that appropriate consent is in place to access any personal information about the participant which is necessary for the quality control of the study.

Additional information on data processing and storage of documents and data is available in Additional file 3 (see
*Extended data*)
^
49
^.

## Monitoring, audit and inspection

### General organisation

The Sponsor (LSHTM) will ensure the safety and respect of individuals who have agreed to participate in the trial. The Sponsor have in place quality assurance systems for monitoring the implementation of the study at the study sites. To contact the Sponsor, see Additional file 7 (
*Extended data*)
^
49
^.

### Monitoring

The trial will be conducted in accordance with the current approved protocol, International Conference on Harmonisation-Good Clinical Practice (ICH-GCP), each participating country’s relevant regulations and the trial’s written procedures. A monitoring plan will be made based on the risks identified in the risk assessment. The LSHTM Clinical Trials Unit (CTU) or country delegate will monitor the trial to ensure the rights, safety, and wellbeing of the trial participants and to ensure the accuracy of the data. All site investigators will be trained in the trial procedures and have extensive guidance. LSHTM CTU will require investigators and their institutions to provide access to source data and documents and all trial related documents for monitoring, audits, ethics committees review and regulatory inspection. All trial-related and source documents including medical records, original consent forms and original CRFs must be kept safely. Investigators must plan in advance of the trial start where the trial-related documents will be stored and how they will be accessed. All documents must be made available when required for monitoring/audit/inspection during the course of the trial and for up to 10 years after the end of the overall trial.

### Audits/inspections

The Sponsor will also be responsible for auditing all aspects of the trial. The site Principal Investigators (PIs) agree to accept the quality assurance audits carried out by the Sponsor as well as the inspections carried out by relevant RECs and regulatory authorities to ensure adherence to the protocol, GCP and relevant regulations.

## Ethical and regulatory considerations

### Consent

Please see the section “Methods for informing and obtaining consent” for details on methods for informing and obtaining consent from the research participants.

### Insurance

LSHTM accepts responsibility attached to its sponsorship of the trial and, as such, would be responsible for claims for any non-negligent harm suffered by anyone as a result of participating in this trial. The indemnity is renewed on an annual basis and LSHTM assures that it will continue renewal of the indemnity for the duration of this trial.

### Access to the final trial dataset

Each site will have continuous access to their own data as the trial is ongoing. The final dataset will be reviewed and published by group authorship consisting of members of the Protocol Committee and key participating site collaborators.

Once all pre-planned analyses are completed, the totally anonymised dataset, protocol, published manuscript, data dictionary and any other relevant trial documents will be made freely available on the
LSHTM CTU data platform.

## Dissemination policy

### Dissemination policy

As Sponsor, LSHTM has the right and responsibility to ensure the results of this study are published. The main publication will be done as a group authorship consisting of the Protocol Committee. Once the pre-specified analysis is completed and data made freely available, anyone can use the trial data.

A final study report will be to be sent to the relevant regulatory authorities and ethics committees within one year of the end of the trial.

There are no plans to notify all participants of the outcome of the trial. However, participants can request a copy of the final results and each site will maintain a log of participants/families who would like a copy. LSHTM CTU provide copies to each site to send onwards.

### Authorship eligibility guidelines and any intended use of professional writers

This study is being conducted as an academic collaboration. All parties who contribute significantly to this study will be named in the final publication.

Professional medical writers will not be hired to write dissemination material about the results of this trial.

## Roles and responsibilities

### Role of trial Sponsor and funder

The funders had no role in the design of the trial and will not have a role in its conduct, data collection, analysis, and interpretation, manuscript preparation, review, and approval, and publication of the results. The Sponsor is responsible for the approval of any substantial amendment which may be needed to the protocol. After approval is given, the Sponsor must obtain, prior to implementing the amendment, approval from the relevant regulatory authorities and ethics committees. The Sponsor is responsible for reporting serious adverse events as per each country’s requirement and all serious breaches to relevant regulatory authority and ethics committees.

### Roles and responsibilities of trial management groups and individuals

**Protocol Development Committee:** This includes the Chief Investigators (CIs), site PIs and participating clinicians and study staff. Its role is to ensure that the study protocol is scientifically appropriate and that all ethical, regulatory and scientific aspects of the trial have been considered. If the protocol requires amending, this committee will review and recommend any changes. The final decision for any amendment to the protocol resides with the Sponsor.

Members of the Protocol Development Committee:

•    [name]: Study design, drafting and finalising the protocol

•    [name]: Study design, drafting and finalising the protocol

•    [name]: Study design

•    [name]: Pharmacokinetic methods and analysis

•    [name]: Study design and drafting the protocol

**Data Monitoring Committee (DMC):** The primary responsibility for monitoring and final decisions about safety of participants in the trial lies with the Sponsor. Independent oversight of the safety of participants will be provided by an independent DMC. The composition of the DMC is provided in Additional file 8 (see
*Extended data*)
^
49
^.

The DMC will review on a regular basis accumulating safety data (adverse events and injection site reactions) from the ongoing trial, and advise CIs regarding the continuing safety of current participants and those yet to be recruited. Data on the type, frequency and severity of adverse events in mother and neonate will be reported to the DMC.

The DMC membership includes expertise in clinical trials, the use of TXA in obstetrics and gynaecology, care of women during childbirth and postnatal period and care of the newborn. The committee members are familiar with the safety profile of the drug.

The DMC Charter includes, but is not limited to, defining:

•the schedule and format of the DMC meetings;•the format for presentation of data;•the method and timing of providing interim reports.

The DMC members are independent of the Sponsor, ethics committees, regulatory agencies, investigators, clinical care of the trial participants, and all trial operations.

**Trial Management Group:** The Trial Management Group will comprise the CI, trial manager, data manager and statistical expert. They will have responsibility for the day to day management of the trial. They will meet regularly to ensure that the trial is progressing according to the protocol.

